## Abstract

**Background:**

In France smoking initiation rates amongst 11 to 16 year-olds are worryingly high. Several studies show that early initiation to psycho-active substances is a strong predictor of tobacco addiction. Decreasing the age at which tobacco use starts represents a key challenge for reducing tobacco usage. Implementing an intervention trial using educational workshops based on the Theory of Planned Behavior (TPB) and covering the 4 years of secondary school could be effective.

**Methods:**

“PEPITES” is an interventional research, using a cluster randomized design. It will allow assessing the effectiveness of interventions both in reducing the tobacco initiation rate and the regular smoking rate of secondary school pupils. We will also evaluate the process of the implementation of the study and thus will help to the transferability of the intervention.

A partnership convention was signed between the JDB Foundation and the National Education authority which designated 6 secondary state schools for the PEPITES trial.

The 6 schools were randomly allocated to 3 groups of 2 clusters each: 1 control group, 2 different intervention groups with 2 workshops per year during 4 years; In one of this group the 2 last workshops will be dedicated to measure the loss of taste due to tobacco smoking. In each school, all pupils in year 1 with a signed parental authorization (744 pupils) have been included in the trial. The interventions targets one of the variables of the TPB and the reinforcement of psycho-social competencies. We estimated that we could detect a reduction of increase ≥5.5 and 8**%** respectively in the 2 principal outcomes (risk α of 5%, and β of 80%).

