### Power of the study

The number of pupils that could be included in the trial is around 750 split into 3 groups of the same size: one control group (T), 2 intervention groups: (A) without EGM experimentation and (B) with EGM use in years 3 and 4. We calculated the rate of reduction of increase in the 2 principal outcomes we could detect, with a global risk α of 5%, a risk β of 20% and an intra-cluster correlation coefficient of “starters and regular smokers” at base line of 0,020 (one-sided test).Comparison Control (T) versus Interventions (A + B) at the end of year 2 on the reduction in increase of *“tobacco use initiation*” (where the increase rate in Essonne is around 10% at the end of the 2 first years of secondary school), and considering that the intervention group A + B (N1) will included ±500 pupils and the control group T (N2) ± 250 (N1/N2 = ½), a significant reduction **≥5.5%** could be detected**.**For the «regular smokers» criterion (where the percentage is estimated at 5% in Essonne at the end of year 2 and 10% in year 4), a significant reduction ≥**4%** at the end of year 2 and **≥ 6.5%** at the end of year 4 could be detected .Comparison 2 by 2 of each of the 3 groups (a control group and 2 intervention groups), for the final analysis at the end of year 4, we will be able to demonstrate a significant reduction increase **≥10%** of “starters” (from the present 25% rate) and a reduction **≥8%** of regular smokers (from the present 10% rate) .

Taking into account in the analysis the factors linked to these 2 outcomes and using appropriate multiple regression analysis and multi-level modeling should allow for an increase in power.

In order to reduce loss of power, the number of pupils lost to follow-up (final questionnaire not filled in at the end of year 2 or year 4) will be minimized by actively searching for them if absent at the time of completing the questionnaire or through the organization of catch-up educational workshops whenever possible.

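### The Abstract prints β as 80% where Power of the study has β 20%; correct the label, and re-run the detectable effects before restating them

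*Protocol article*

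**What the plan says.** The Methods paragraph of the Abstract says: "We estimated that we could detect a reduction of increase ≥5.5 and 8" per cent, assigned in that order to the two principal outcomes, with "risk α of 5%, and β of 80" per cent.

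Power of the study derives the same two figures "with a global risk α of 5%, a risk β of 20" per cent, and with an intra-cluster correlation "at base line of 0,020 (one-sided test").

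- The 5.5 belongs to "Comparison Control (T) versus Interventions (A + B) at the end of year 2", for initiation, where "the increase rate in Essonne is around 10% at the end of the 2 first years of secondary school". Its sample sizes are given as "the intervention group A + B (N1) will included ±500 pupils and the control group T (N2) ± 250 (N1/N2 = ½").
- The 8 is for regular smoking in the fourth year, from a rate of 10%, under the item that opens "Comparison 2 by 2 of each of the 3 groups (a control group and 2 intervention groups), for the final analysis at the end of".

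Outcomes measures gives each principal outcome its own comparison. Experimentation is compared between the two intervention groups pooled and control, at the end of years 2 and 4. Regular smoking is compared pairwise between the three groups at the end of year 4.

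**The concern.** β is the type II error. An Abstract that puts it at 80% says the trial would miss the stated effects four times in five, while the body of the article says one time in five. Both statements are attached to the same two reductions, so they cannot both be right. Many readers will take the trial's power from the Abstract alone.

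Two further features of the power text add to the doubt. The printed allocation ratio is the reciprocal of what the adjacent group sizes give. The Abstract's two figures also come from different comparisons and different years, without saying so. Power of the study gives two figures for regular smoking at the end of year 4, 6.5 and 8, so a reader of the Abstract cannot tell which comparison the 8 refers to.

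Once β is read as 20%, the remaining question is whether 5.5 and 8 are the effects detectable at 80% power under the stated inputs. If they are not, correcting the label would put a clean statement on an unsupported figure.

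**Working it through.** **Inputs.** From Power of the study: α 5%, one-sided; β 20%; ICC ρ = 0.020; control rate 10% for both outcomes; 250 control and 500 pooled intervention pupils; 250 per group for pairwise comparisons (about 750 in three equal groups). From Study population: 744 pupils, 33 classes, 6 schools, hence 744/6 = 124 per school and 744/33 = 22.5 per class. Reductions are read as percentage points; a relative 5.5% of a 10% rate would be only 0.55 points, far too small for a trial of this size.

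**Label and ratio.** β 80% means power 1 − 0.80 = 20%. N1/N2 = 500/250 = 2, and N2/N1 = ½.

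**Formulas.** With Δ = p1 − p2 and p̄ the weighted mean rate:

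- s0 = √[p̄(1 − p̄)(1/n1 + 1/n2)]
- s1 = √[p1(1 − p1)/n1 + p2(1 − p2)/n2]
- power = Φ[(Δ − z·s0)/s1], with z = 1.645 one-sided or 1.960 two-sided
- clustering: divide each n by DEFF = 1 + (m − 1)ρ, which is 1 + 123 × 0.02 = 3.46 for schools and 1 + 21.5 × 0.02 = 1.43 for classes

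**Trying to reproduce 5.5.** p1 = 0.10, p2 = 0.045, p̄ = (25 + 22.5)/750 = 0.0633. Without clustering, s0 = 0.01887 and s1 = 0.02112.

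- One-sided: (0.055 − 0.03104)/0.02112 = 1.135, power 87.2%.
- Two-sided: (0.055 − 0.03698)/0.02112 = 0.853, power 80.3%. The required control group is 248, against 250 available.

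Of the variants tried with this formula, the printed 5.5 matches 80% power only with a two-sided test and no clustering. Neither is what the section states.

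**Does the ratio matter?** With the sizes swapped (control 500, intervention 250), two-sided and unclustered, 5.5 points has 76.3% power. The effect detectable at 80% power moves from 5.48 to 5.70 points two-sided, or from 4.98 to 5.12 one-sided. The printed 5.5 fits the correct sizes better than the swapped ones.

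**Stated inputs, ICC at school level, one-sided.**

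- 5.5 points: effective sizes 250/3.46 = 72.3 and 500/3.46 = 144.5; s0 = 0.03509, s1 = 0.03928; (0.055 − 0.05772)/0.03928 = −0.069; power 47%.
- 8 points: p2 = 0.02, p̄ = 0.06; s0 = 0.03951, s1 = 0.03895; (0.08 − 0.06499)/0.03895 = 0.385; power 65%.

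Power and detectable effect, one-sided 5%:

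| Effect | No clustering | Class level | School level | Points needed for 80% power, school level |
|---|---|---|---|---|
| 5.5 points, initiation, pooled, year 2 | 87% | 76% | 47% | 8.1 |
| 8 points, regular smoking, pairwise, year 4 | 98% | 94% | 65% | 9.3 |

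**Testing the literal reading.** At 20% power, with school-level clustering, the detectable effects would be about 3.0 and 3.7 points. The printed 5.5 and 8 therefore do not come from a 20% power target with these inputs.

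**The case against.** The strongest reply is that these are two typographical slips. Power of the study is the full statement and gives β correctly. Nothing there targets 20% power, and no sample size, analysis or conduct depends on the Abstract. The group sizes stand in the same clause as the wrong ratio, so anyone repeating the calculation has the right inputs. This stands: β 80% is a labelling error, and a reader who inferred that the trial was designed to have 20% power would be going beyond the documents. The documents also give no sign that the wrong ratio was used, since 5.5 fits 250 controls against 500 better than the reverse.

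A reader might further infer that the Abstract wrongly mixes a pooled year-2 figure with a pairwise year-4 figure. Outcomes measures does not support that. It assigns the pooled comparison to experimentation and the pairwise year-4 comparison to regular smoking, so listing 5.5 and 8 in that order follows the definitions. Leaving out the other figures in Power of the study is ordinary condensation. What remains is a lack of labels.

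It can also be said that clustering is a separate matter from a misprinted β. But the correction itself restates 5.5 and 8 as effects detectable at 80% power, and the stated inputs do not give that. The level at which the ICC was meant to apply is not stated, so the size of the shortfall is uncertain. Schools are the randomized unit, which makes school level the natural reading, but class level is shown beside it.

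**Conclusion.** The Abstract's power statement is wrong as printed: β should read 20%, as in Power of the study. The ratio N1/N2 = ½ is inverted, but it shifts the detectable effect by only 0.14 points one-sided or 0.22 two-sided. The pairing of 5.5 with 8 is sound but unlabelled.

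The corrected sentence would still not be supported by its own inputs. At school level, 5.5 and 8 points have about 47% and 65% power, and 80% power needs about 8.1 and 9.3 points. At class level the powers are 76% and 94%, so even then neither figure is the effect detectable at 80%: the first falls slightly short and the second is conservative.

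These results assume absolute reductions from a 10% control rate, a normal approximation, equal cluster sizes and no loss to follow-up. Having only two schools per group would lower power further than the design effect shows.

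**What to change.** 1. In the Abstract, write β of 20% (power 80%).
2. In the same sentence, give each reduction in percentage points with its comparison and year: initiation, pooled intervention versus control, end of year 2; regular smoking, pairwise, end of year 4.
3. In Power of the study, print N1/N2 = 2 (or N2/N1 = ½) and confirm which sizes were entered.
4. Before restating 5.5 and 8, re-run both with the stated one-sided 5% test and ICC of 0.020. State the level at which the ICC applies and the cluster size used, and print the resulting effects.

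The cost is a few words and one short calculation. Recruitment, intervention and data collection are not affected.

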**Discussion:**

Carrying out a randomized prevention trial in the school environment raises specific problems which it seems useful to detail for other educational actors who would like to perform a similar study.

This discussion concerns the acceptation and cooperation of the National Education partners, the risks of contamination, the information given to parents and pupils and their consent, and the representativeness of the schools involved.

**Trial registration:**

ISRCTN85812512. Registered 15 May 2018 by BioMed Central. (retrospectively registered).

## Background

In France smoking initiation rates amongst 11 to 16 year-olds continue to be worryingly high, with however some positive indicators in the Ile-de-France Paris region (IDF) compared to the rest of the French mainland [1]. With the age of first tobacco smoking between 12 and 14 years old and the age of daily tobacco use between 14 and 16 years old, it is clear that young people who have not tried tobacco are in the minority at high school: in IDF at the age of 17, near 63% have already tried tobacco and 27% smoke every day [2]; in the Essonne department (IDF) at the age of 17, 23% were smoking every day in 2011 [3]. If, in the early 2000s, tobacco usage was falling, the numbers have since leveled off, as demonstrated by the 2011 and 2014 Escapad surveys [4]. In this context, the French Social Affairs Ministry launched a national policy to try to reduce the number of people smoking daily to below 20% by 2024 [5]. The means to achieve this reduction focus in particular on actions directed at younger people. In France, until now, few actions have been effective in pushing back the age at which tobacco is first consumed and in reducing tobacco addiction amongst young people.

Many international programs, which aim to reduce tobacco consumption in young people, are carried out in the school environment, and, by doing so, they are able to address a more or less «captive audience» as well as to monitor the actions and outcomes over a period of several years [6, 7]. The approaches which have been identified as promising involve putting in place a tobacco prevention pathway throughout the entire school years with various annual sessions incorporated in the school program and conducted by professionals from outside the school. These sessions consist of workshops based on behavioral modulator theories and on the increase of the psychosocial competencies of the school children [8] support from parents and school personnel (« zero cigarette » policy in school and outside school, help to stop smoking) might increase the effectiveness of tobacco prevention actions amongst young children [9].

Several studies show that early initiation to psycho-active substances (tobacco, cannabis, alcohol) is a strong predictor of tobacco addiction [10]. Early initiation leads to stronger addiction and a lower ability to stop smoking [10]. Signs of nicotine dependence appear right from the first weeks of consumption by young people [11].

Increasing the age at which tobacco use starts represents a key challenge for reducing tobacco usage by the population later in their lives . A study carried out in the French Languedoc-Roussillon region showed that there are two key moments in the evolution of smoking amongst youngster: initiation between 12 and 13 years old (5th and 4^th^school levels) and established habit between 15 and 16 years old (3rd and 2nd levels) which leads to addiction [12]*.*

Furthermore it has been clearly demonstrated that, in order for prevention actions to be effective, they need to be repeated regularly; one action alone, outside of the usual environment, has little chance of changing the behavior of individuals in the long term.

Considering all of the above points, the present intervention trial on tobacco prevention covering the 4 years of secondary school (11 to 15 years old) was implemented in the Essonne department where the JDB Foundation for Cancer Prevention is based. This trial is based on a cluster randomization trial design comparing 3 groups: two intervention groups and a control group, thus allowing a better evaluation of the effectiveness of the interventions.

Within the scope of the proposed educational workshops based on the theory of planned behaviors (TPB) [13, 14]; we also test the hypothesis that the concrete and measurable discovery by pupils of sensory modifications rapidly provoked by tobacco, such as loss of taste, might lead to a better understanding of the harmful effects of tobacco. This might increase the motivation of young people to not start smoking or to stop consuming. This paper describe the protocol of the PEPITES trial (**P**rogram in **E**ssonne for the **P**revention of the **I**nitiation to **T**obacco through **E**ducation in the **S**chool environment), and its implementation in 6 secondary schools in the Essonne department.

## Methods

### Aims and study design

PEPITES is an interventional research study in primary prevention, using the cluster randomized trial design. This methodology will allow assessing the effectiveness of the interventions both in reducing the tobacco initiation rate and the regular smoking rate of secondary school pupils. We will also evaluate the process of the implementation of the study *(*what works, for whom, for what and in what circumstances) and thus will help to the transferability of the intervention [15].

Randomized cluster is used where individual randomization is not ethically possible: all pupils in the same class, or of the same level of class of a given secondary school, must enjoy the same supposed beneficial activities for their health*.* Additionally this technique avoids contamination, that is that randomized pupils in the control arm be influenced by pupils from the intervention arm and change their behavior spontaneously [16] .

This research protocol has been validated by the Consultative Committee for Information Processing in relation to Research in the Health field (CCTIRS) previously to obtain the mandatory CNIL (Commission Informatique et des Libertés) authorization and by the Ethical Evaluation Committee of INSERM (Institut National de la Santé et de la Recherche Médicale).

### Population selection and randomization

A partnership convention was signed between the JDB Foundation and the Essonne National education authority which designated 6 secondary mixed sex state schools for the PEPITES trial as part of their commitment to health education.

After this designation and before randomization, school head teachers were sent detailed information of the study protocol, followed by a visit by study team members. Then a member of the school management was designated to be the key contact for the study investigators.

The randomization process was carried out by a study investigator during a meeting organized at the JDB Foundation where representatives of each secondary school were present.

The 6 schools were allocated to 3 groups of 2 clusters each (Fig. 1):one group of 2 secondary schools with 2 educational workshops per school year; that is 8 interventions per secondary school over the 4 years,one group of 2 secondary schools with 2 educational workshops per school year; that is 8 interventions per secondary school over the 4 years, with one of the workshops dedicated to measure taste with the electrogustometer during the 3rd and 4th years,

**Fig. 1 Fig1:**
[figure not shown]
PEPITES trial design

All the educational workshops were carried out by the JDB Foundation professional prevention trainee;one control group of 2 secondary schools with no intervention planned by the JDB Foundation.

### Study population

In each secondary school, all pupils in year 1 (grade 6) at the time of the survey, with a signed parental authorization form (94% of year 1 pupils), have been included in the PEPITES trial.

Written parental authorization was requested for the whole duration of the trial after sending a letter which outlined the principal objectives of the trial and the intervention undertaken. The pupils could also refuse to participate even if the parents had given their authorization.

At the start of the study in September 2014, the included population was 744 pupils covering 33 classes in the 6 secondary schools and were expected to be followed, during the 4 years of secondary school.

### Proposed educational interventions

The proposed interventions targets one of the variables of the TPB (i.e., attitude, subjective and social norms, perceived control and intention) and the reinforcement of psycho-social competencies (resistance to pressure, critical mind, reasoned choice, civil responsibility). Teaching methods are based on inter-activity and practical experimentation.➢ The educational sessions are adapted to the age of the pupils, tested and conducted by prevention professionals from the JDB Foundation. They are carried out during school time and last 45 min. In chronological order they cover the following themes: reasons for starting smoking, awareness of the risks taken, explanation of the marketing strategies of the tobacco industry, the mechanism of addiction and the effects on health (Table 1).➢ Experimental session measuring taste change linked to tobacco use. Our hypothesis is that the concrete consciousness of the harm caused by tobacco use could increase children awareness regarding the harmful effects of tobacco and consequently improve their motivation to not start smoking or to stop if they have started. A tool, the electrogustometer (Fig. 2), makes it possible to measure the taste sensitivity of the tongue - sensitivity which reduces significantly for a smoker from the first cigarette regularly smoked [17].

**Table 1 Tab1:** Content of educational sessions

Year 1 (Age ± 11): Why do people start smoking?	
ᅟThink about the reasons for starting smoking and be aware of the space tobacco occupies in our society today (Peer pressure).	
ᅟAt the end of the workshop, the pupils should be able to: ᅟᅟ− Think about what influences a person to start smoking (or not) ᅟᅟ− Expose the major lines of the history of tobacco in our society	
Year 2 (Age ± 12): Risk behavior, Stress management, Risk taking and alternatives	
ᅟThink about what risks they take in their daily lives	
ᅟAt the end of the workshop, the pupils should be able to: ᅟᅟ− Explain what constitutes risk behavior ᅟᅟ− Imagine alternatives to risk taking	
Year 3 (Age ± 13): Manipulation by the tobacco industry – Marketing strategy	
ᅟDevelop a critical mind by analyzing sales techniques and influencing techniques of the tobacco industry	
ᅟAt the end of the workshop, the pupils should be able to: ᅟᅟ• Discuss the main determinants in the regular consumption of tobacco ᅟᅟ• Quote the marketing strategies used by the tobacco industry	
Year 4 (Age ± 14): Tobacco: Effects and addiction	
ᅟReinforce knowledge on addiction	
ᅟAt the end of the workshop, the pupils should be able to: ᅟUnderstand the link of dependence between a smoker and his tobacco ᅟDescribe the effects of tobacco on the body organs.

**Fig. 2 Fig2:**
[figure not shown]
Electrogustometer (Unpublished figure: created by the authors for this manuscript)

In the second intervention group, during years 3 and 4, one educational session is dedicated to the use of the electrogustometer, and to observe results of pupils who are smokers or non-smokers.

### Outcomes measures

#### Evaluation of the results

The 2 principal outcomes for the PEPITES trial are:The prevalence of pupils having experimented (at least once) tobacco smoking at the end of year 2 and year 4 as compared to beginning of year 1 (comparison of the 2 intervention groups together versus the control group)The prevalence of regular (at least weekly) cigarette smokers at the end of year 4 (comparisons of the 3 groups 2 by 2).These outcomes will be collected at the beginning of each year and at the end of year 2 and 4, and their evolution over time analyzed in each of the groups and compared. Outcomes prevalence measures are only based on pupils declaration.The secondary outcomes include experimentation with hookah, cannabis, electronic cigarettes, perception of norms, attitudes and future intentions of the participants with regard to smoking.

The various determinants which may have a role in starting smoking or becoming a regular smoker (gender, siblings, sporting activity, home area (ZUS), smokers in the entourage (parents, friends…) will also be studied and reported.

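### The protocol article does not fix which year-4 contrast decides each principal outcome, and its pairwise detectable differences fall well short of the stated 80% power

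*Protocol article*

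**What the plan says.** - **Design (Population selection and randomization):** "The 6 schools were allocated to 3 groups of 2 clusters each". Call them T (control), A (workshops) and B (workshops plus taste measurement in years 3 and 4).
- **Outcome definitions (Evaluation of the results):** experimentation, at the end of years 2 and 4, is a "comparison of the 2 intervention groups together versus the control group". Regular smoking is "The prevalence of regular (at least weekly) cigarette smokers at the end of year 4 (comparisons of the 3 groups 2 by 2".
- **Power of the study:** the calculation starts from this premise: "The number of pupils that could be included in the trial is around 750 split into 3 groups of the same size". It works "with a global risk α of 5%, a risk β of 20"%, and takes the intra-cluster correlation "at base line of 0,020 (one-sided test"). Under the T versus A+B item it gives 5.5 points for initiation at year 2, and 4 points (year 2) and 6.5 points (year 4) for regular smoking. It then turns to "Comparison 2 by 2 of each of the 3 groups (a control group and 2 intervention groups), for the final analysis", with 10 points for starters from 25% and 8 points for regular smokers from 10%.
- **Statistical analysis:** both principal outcomes are compared at year 2 in two groups and at year 4 in two and in three groups, by logistic regression models that account for clustering.

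**The concern.** At year 4 the three sections give three different sets of contrasts:

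| Section | Experimentation, year 4 | Regular smoking, year 4 |
|---|---|---|
| Evaluation of the results | pooled only | pairwise only |
| Power of the study | pairwise only | pooled and pairwise |
| Statistical analysis | two and three groups | two and three groups |

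A reader cannot tell which year-4 result decides success on either outcome, so the choice could be made after the data are seen.

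The outcomes section also gives the rarer outcome the less sensitive contrast. By the article's own figures, pooling detects 6.5 points from a 10% rate, while a pairwise comparison needs 8. Each pairwise comparison sets two schools against two. If the power claimed for those comparisons is not there, a real effect on regular smoking would probably be missed, and a null result would be read with more confidence than it deserves.

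**Working it through.** **Inputs.** About 750 pupils in three equal groups gives 250 per group and 125 per school (the included number, 744, gives 124). ICC 0.02, one-sided 5%, target power 80%. Year-4 control rates are 10% (regular smoking) and 25% (starters).

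**Assumptions.** Reductions are in percentage points. The ICC applies to schools, the randomised units. Schools are equal in size, with no attrition. Each test gets the full 5%, which favours the plan because its 5% is described as global.

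**Design effect.** 1 + (125 − 1) × 0.02 = 3.48, so 250 pupils count as 250 / 3.48 = 71.8.

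**Attempt to reproduce the stated figures** (two-proportion z-test with pooled variance under the null, solved for 80% power):
- With the stated inputs, the pairwise detectable reduction from 10% is 9.3 points, not 8; power at 8 points is 65%. The pooled one is 8.1 points, not 6.5; power at 6.5 points is 60%.
- With no clustering and a two-sided 5% test, the initiation figures come back (5.48 and 10.0 points, stated as 5.5 and 10). Regular smoking gives 5.5 (pooled) and 6.3 (pairwise), not 6.5 and 8.
- With the class as cluster (744 / 33 = 22.5 pupils, design effect 1.43) and a two-sided test, regular smoking gives 6.3 and 7.3.

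No single variant gives the full set.

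**Power at the stated pairwise effects.** SE = √{3.48 × [p₀(1−p₀)/n₀ + p₁(1−p₁)/n₁]}, δ = (p₀ − p₁)/SE. Power by z is Φ(δ − 1.645). Power by school-level t comes from the noncentral t with non-centrality δ. Degrees of freedom are 2 using the four schools of the pair (critical value 2.92), or 3 if between-school variance is pooled over all three arms (2.35).
- Regular smoking, 10% to 2%: SE = √{3.48 × (0.0900 + 0.0196)/250} = 0.0391; δ = 0.08/0.0391 = 2.05.
- Starters, 25% to 15%: SE = √{3.48 × (0.1875 + 0.1275)/250} = 0.0662; δ = 0.10/0.0662 = 1.51.

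| Pairwise effect | z | t, 2 df | t, 3 df |
|---|---|---|---|
| 10% to 2% | 66% | 40% | 47% |
| 25% to 15% | 45% | 27% | 32% |

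(The 66% uses unpooled variance; the 65% above uses pooled variance.)

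**The pooled contrast, 500 against 250** (four schools against two, 4 df, critical value 2.13):
- 10% to 2%: SE 0.0373, δ = 2.15, power 55%.
- 10% to 3.5% (the article's own 6.5 points): SE 0.0386, δ = 1.69, power 40%.
- 25% to 15%: SE 0.0591, δ = 1.69, power 41%.

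The 4 df assume that A and B share one mean. On 3 df the three powers are 50%, 37% and 37%.

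**Randomisation floors.** Two schools against two allows C(4,2) = 6 allocations, so the smallest exact one-sided p is 1/6 = 0.167. Four against two allows C(6,2) = 15, so it is 1/15 = 0.067.

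**The case against.** **The pooled test is already planned.** A reader of the outcomes section alone might infer that regular smoking is tested only pairwise. The documents do not support that. The statistical analysis section includes a two-group comparison of both outcomes at year 4, and the power section gives a pooled figure for regular smoking. The fault is inconsistency, not an absent test.

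**Significance is not out of reach.** From the 1/6 floor one might infer that a pairwise comparison can never be significant. That floor binds only an exact test permuting the four schools of a pair, and the article names no such test. It plans clustered logistic and multilevel models, which can return p < 0.05, and the t-test power of 40–47% shows the same. The same argument would disqualify the pooled contrast, whose floor of 1/15 also exceeds 0.05.

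**Pairwise may be deliberate.** A and B differ only in years 3 and 4, so separating them at year 4 follows from the design, and the Abstract quotes the 8-point pairwise figure for regular smoking. Pooling is better only if A and B work similarly. As an illustration, if B lowers regular smoking from 10% to 2% and A does nothing, the pooled contrast is 10% against 6% with about 21% power, against about 47% for B versus T on 3 df.

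All of this stands. It limits the point to reconciling the sections and correcting the power claims, and it makes the choice of pooling a judgement. It does not explain why the three sections differ, and it does not restore the 80% power. The article also expects covariate adjustment and multilevel modelling to raise power, but it attaches no figure to that gain.

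**Conclusion.** The concern holds in this form: the year-4 principal contrast is stated differently in three sections, and the pairwise detectable differences are not supported by the article's own ICC, school size and error rates. Instead of 80%, pairwise power is about 66% (regular smoking) and 45% (starters) by z, and about 40–47% and 27–32% by school-level t.

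The size of the shortfall depends on applying the ICC of 0.02 to schools of about 125. With classes as clusters the regular-smoking figures would be roughly met, but classes were not the units randomised. Attrition or a split of the global 5% across comparisons would lower power further.

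Pooling helps only modestly. For 10% to 2% it gives 55% on 4 df against 40% (2 df) or 47% (3 df) pairwise, and on 3 df for both it is 50% against 47%. The root limit is two schools per group, which affects both principal outcomes and which no rewording removes.

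**What to change.** 1. In Evaluation of the results, name A+B versus T as the year-4 principal contrast for both outcomes. Statistical analysis already plans it, and Power of the study already gives a figure for regular smoking.
2. Make A versus T, B versus T and A versus B secondary. Report each as a difference with a confidence interval from school-level data, with between-school variance pooled over the three arms (3 df), and make no confirmatory claim.
3. In Power of the study, restate the detectable differences, or the power at the present ones, with the design effect, test and degrees of freedom shown. Add the missing pooled figure for year-4 experimentation, and say that pooled power remains about 40–55% at these effects.
4. Align Statistical analysis and the Abstract with this. Date the change, and state whether any year-4 outcome data had been seen.

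The cost is wording only: no new schools, pupils or data. What is given up is a confirmatory claim for A or B alone, and sensitivity if only one of them works. If the investigators prefer to keep a pairwise principal contrast for that reason, they should name which one, give its actual power, and make all three sections agree.
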